#### Research impact

For assessing research impact, we will use the Framework to Assess the Impact from Translational health research (FAIT). This framework includes metrics and a program logit structure. This tool is based on a modified program logic model that includes evaluation process, outputs, measurements of impact and process metrics (including research activities and research translation).

Additionally, end of study interviews will be conducted with Managers, Champions, and Health Care Practitioners. The interview guide will be designed based on the COM-B model.

#### Micro-costing analysis

A prospective micro-costing analysis of the implementation of the Evaluation-Research package (Option 1) will be conducted, including the design cost, initiation, and maintenance of the project. To estimate the cost, we will include the following information:

Design of the intervention and its promotion cost that includes the cost of the design of the e-Learning toolFeedback from experts: Estimation of cost of meetings with different panels of expertsiSISTAQUIT Staff costs: Cost of recruitment, training, implementing the intervention and follow upHealth service costs: cost of appointments (number and duration of them), cost of training estimated by the duration of the training, cost of follow up meetings with the iSISTAQUIT team, among others.Intervention: material for the intervention (cost of time spent on the eLearning training printed material, eLearning design costs and website platform, NRT cost, smokerlyzers, etc)

#### Outcome measures related to social media campaign

Engagement, awareness and effectiveness of the social media campaign will be measured through a combination of methods including assessment of social media metrics of online content released by the campaign as well as surveys and qualitative interviews with stakeholders including health care providers, Aboriginal and Torres Strait Islander women and community members. More details are available from Table 3.

**Table 3 pone.0274139.t003:** Evaluation of social media campaign.

Characteristic	Details
**Target population**	Aboriginal and Torres Strait Islander audience exposed to the social media campaign including pregnant women, other women of reproductive age, their family members, their social contacts, and health care providers catering to Aboriginal women in pregnancy.
**Study design**	Survey, post-survey interview/focus group and social media surveillance
**Recruitment**	Aboriginal community participants will be recruited via social media (through active calls for participation via iSISTAQUIT and collaborators’, panel members’ and supporters’ websites and social media pages), participant interception at iSISTAQUIT study sites and community events. Participants will be asked to share the survey with others, or recommend them to take the survey, through snowball recruitment.
**Sample size**	If 50% of participants have heard of the campaign in the post period, a sample of 100 women from the iSISTAQUIT sites will enable estimation of this proportion with a 10% margin of error. Sample size for qualitative interviews will depend on numbers needed to attain data saturation.
**Data collection and outcome measures**	**Surveys:** To assess engagement, awareness and effectiveness of the social media campaign and related branding in influencing knowledge, attitudes and beliefs of pregnant women who smoke. **Qualitative interviews or focus groups:** conducted after about 3–6 months of campaign initiation with women, community members and Health Providers. A semi-structured interview schedule will be used to steer the interview/focus group discussion. Below are some examples of the questions included in the schedule: • What did you like about the campaign? What are we doing well? What should we continue to do? • What are we doing okay or badly with the campaign? • What we could have done instead? • Do you have any likes/dislikes / suggestions about the videos? • Have the videos changed your views or behaviour in any way? • Did you learn anything new? **Both surveys and interviews will be conducted together via personal intercept at the study sites.** **Social media metrics:** Social media metrics will be directly tracked and recorded from the social media webpages using platform specific social media tracking. IndigenousX will deliver these metrics in a detailed report. This will demonstrate the effectiveness of the campaign with the intended audience and the public. Google analytics will be used to profile the characteristics of the audience. Following metrics will be summarised both overall and by month: **Engagement**: Counts of retweets, likes, comments, link clicks, mentions, and direct messages received. **Content sharing**: Counts of testimonials, shares, reviews, guest posts, shared pictures at monthly intervals throughout the campaign **Audience characteristics**: Counts of total followers, new followers. This will also be broken down by users’ sex and age and location (Google analytics). **Content utilisation:** a) analysing comment sentiments (positive, neutral, or negative as supplied by IndigenousX), b) summary statistics of website utilisation will be presented, including the number of website sessions, total page views, bounce rate (single-page sessions divided by the number of total sessions on the website), pages per session, average session duration, mobile vs. desktop traffic.
**Analyses**	***Surveys*:** Surveys will be analysed descriptively. ***Social Media Metrics*:** Descriptive and summary statistics will be used to analyse trends in social media metrics. Regression analysis will be used determine the relationship between the user characteristics (e.g., age, sex, region etc.) and social media metrics. ANOVA/t-tests or their non-parametric counterparts will be used to assess if there are statistically significant differences in user engagement (e.g., number of likes, shares etc.) across different social media platforms. We will conduct a qualitative sentiment analysis of textual content (comments, tweets, post from users and direct messages) posted on the social media pages to classify the emotions expressed by the users in these posts. Textual content will also be analysed using thematic analysis to identify predominant themes, which will then be used to tailor the content posted on the social media and iSISTAQUIT website to improve user engagement and useability of the webpages. **Qualitative interviews/ focus groups:** Focus groups and interviews will be audio-recorded and transcribed followed by thematic analysis.

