#### Social media campaign

The research component of the social media campaign is being conducted from December 2021 to September 2022. After this date, the social media campaign may continue in a non-research capacity. The aims of the social media campaign are: to increase iSISTAQUIT brand recognition, increase awareness about smoking cessation for Aboriginal and Torres Strait Islander women in pregnancy, increase interest about the program and promote behaviour change among Aboriginal and Torres Strait Islander communities and health professionals. The creative approach for the social media campaign will be developed by the company Gilimbaa in partnership with IndigenousX who will be developing the social media strategy to deliver a comprehensive campaign. Gilimbaa and IndigenousX are Aboriginal owned and operated media, consultancy, and training organisations. This national campaign will consist of systematic advertising and promotion of iSISTAQUIT and video messages through various social media platforms that will be set-up, such as Facebook, Instagram, LinkedIn, and, Twitter. An Aboriginal owned company Ngakkan Nyaagu (NGNY) is developing an iSISTAQUIT website. The primary focus for distribution of the social media campaign will be through the early adopter service states namely Queensland, New South Wales, and South Australia. The ongoing management of the website and social media accounts will be led by Southern Cross University and will be updated regularly with advertising content such as professionally produced videos, photos, and posts.

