#### Evaluation plan

iSISTAQUIT training: Evaluation will be done using the RE-AIM framework, which systematically evaluates the Reach, Effectiveness, Adoption, Implementation and Maintenance of implementation studies. For details see, Table 2.

Descriptive statistics will be used to present numbers, rates, proportions and trends in the data collected through surveys, Likert scales and service level data available through data collection tools described in Table 2. Thematic analysis will be used to analyse qualitative data collected during end of study interviews with practitioners, managers and research facilitators at the services.

Knowledge, attitudes and practices related to SCC: Differences in practitioner online survey responses from pre-training (referent period) to immediate post- and 3 months post-training will be assessed using linear mixed effects regression models, including fixed categorical effects for time, and a random intercept for site to model correlated responses for practitioners from the same service.

Social media campaign: The success of social media campaign will be assessed using surveys, qualitative methods, and social media metrics. More details are available from Table 3.

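### The 10% margin of error for campaign awareness is an independent-sample best case that leaves out correlation among women from the same study site

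*Protocol article*

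**What the plan says.** The Sample size row of Table 3 (section on outcome measures for the social media campaign) sets out its premise, "If 50% of participants have heard of the campaign in the post period", and concludes that "a sample of 100 women from the iSISTAQUIT sites will enable estimation of this proportion with a 10% margin of error". It gives no confidence level, design effect, ICC or number of survey sites.

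The same table describes how respondents are found in two ways:

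- The Recruitment row lists calls on social media and "participant interception at iSISTAQUIT study sites and community events", and adds that "Participants will be asked to share the survey with others, or recommend them to take the survey, through snowball recruitment".
- The row on data collection says that "Both surveys and interviews will be conducted together via personal intercept at the study sites".

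On analysis, Table 3 says only that "Surveys will be analysed descriptively". For the separate practitioner survey, the Evaluation plan section includes "a random intercept for site to model correlated responses for practitioners from the same service". Nothing comparable is stated for the women. The Sample size section of the methods plans 20 sites and allows up to 30.

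**The concern.** The precision statement treats the 100 women as independent, but its own sentence draws them from the sites. If awareness differs between sites, women from one site resemble each other and 100 women carry less information than 100 independent ones.

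The article gives some reason to expect such differences. The Social media campaign section concentrates distribution on three states, while the ethics approvals also cover the Northern Territory and Western Australia. Early-adopter services may help make the campaign videos. Sites are a mix of community-controlled and mainstream services.

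The awareness proportion is the only quantity for which the campaign survey is given a sample size. Because the survey is descriptive, the stated precision is the main guide to how firmly the result can be read. If it is too favourable, awareness will be reported with more certainty than the sample holds.

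**Working it through.** **Inputs.** Awareness p = 0.50 and n = 100 (Table 3). Sites k = 20 planned, up to 30 (Sample size section). The k = 10 case is my assumption: the Intervention section limits data collection to services taking the Evaluation-Research package unless otherwise specified, and the planned 20 are not split by package, so fewer than 20 may contribute. The ICC is also an assumption (0.01 to 0.10). The confidence level is not stated; I take 95% two-sided because it reproduces the figure.

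**Step 1: reproduce the stated figure.** Half-width = 1.96 × √(0.5 × 0.5 / 100) = 0.098, or 9.8 points, which rounds to 10. At 90% confidence it would be 8.2 points and at 99% it would be 12.9.

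**Step 2: find the slack.** Exactly 10 points needs 1.96² × 0.25 / 0.10² = 96.04, so 97 women. With 100 women the design effect can rise to 100 / 96.04 = 1.04 before 10 points is exceeded. If any half-width up to 10.5 is accepted as rounding to 10, the limit is (10.5 / 9.8)² = 1.15.

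**Step 3: add site clustering.** With m = 100 / k women per site, the design effect is 1 + (m − 1) × ICC, and the half-width is 9.8 × √(design effect).

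| ICC (assumed) | 30 sites (m = 3.3) | 20 sites (m = 5) | 10 sites (m = 10) |
|---|---|---|---|
| 0.01 | 9.9 | 10.0 | 10.2 |
| 0.02 | 10.0 | 10.2 | 10.6 |
| 0.05 | 10.4 | 10.7 | 11.8 |
| 0.10 | 10.9 | 11.6 | 13.5 |

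Example: 20 sites at ICC 0.05 give 1 + 4 × 0.05 = 1.20, and 9.8 × √1.20 = 10.7 points.

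**Step 4: find the break-even ICC.** At 20 sites, 10 points holds up to ICC 0.04 / 4 = 0.01, or up to 0.148 / 4 = 0.037 on the rounding reading. For scale, a hypothetical split with 60% awareness in half the sites and 40% in the other half gives ICC = 0.1² / 0.25 = 0.04.

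**Step 5: consider what the table leaves out.** A t multiplier on k − 1 degrees of freedom widens the interval further. For ICC 0.01 to 0.10 it gives 10.3 to 11.4 points at 30 sites, 10.7 to 12.4 at 20, and 11.8 to 15.6 at 10. Unequal numbers per site push the same way; I have not put a figure on that. The site formula does not cover snowball referral.

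**Step 6: consequence if clustering were ignored in the report.** Coverage of an independent-sample 95% interval is 2Φ(1.96 / √design effect) − 1. At ICC 0.05 and 0.10 this is 92.6% and 90.2% with 20 sites, and 89.6% and 84.5% with 10 sites.

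**The case against.** There is no arithmetic mistake: the figure is a correct result from a common planning formula. The size of any loss depends on an ICC that the documents do not supply. At 20 to 30 sites with a small ICC, the margin stays at about 10 points. The campaign is national and runs on social media, so exposure is not delivered clinic by clinic, and help with filming is optional and depends on pandemic restrictions. The practitioners' random intercept concerns people trained through their service, which is a different mechanism. The plan prescribes no independent-sample interval, and the method for the interval may sit in a fuller document. No test or decision threshold hangs on this proportion.

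Most of this stands, and it rules out three stronger readings that a reader might infer:

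- **That the 10% is not achieved.** This cannot be said without an ICC. At 20 sites and ICC 0.01 the margin is still 10.0 points.
- **That the true margin is about 11 to 14 points.** The upper end needs both ICC 0.10 and only 10 contributing sites, and the documents state neither.
- **That the 100 women are a snowball sample.** The sample-size sentence ties them to the sites, whereas referral is described for community participants in general. The Recruitment and data-collection rows do not agree, so the make-up of the 100 is unclear.

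What survives is that Table 3 makes a definite precision claim with no allowance for the site-based sampling in the same sentence. Leaving the interval method to another document does not alter that claim.

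**Conclusion.** The point holds in a limited form. The 10% is the 95% independent-sample figure, it has almost no slack, and Table 3 does not present it as a best case. Positive within-site correlation can only widen it. On the normal approximation, with equal numbers per site and ICC 0.01 to 0.10, the widening beyond 10 points is 0 to 1.6 points at 20 sites. It is at most 0.9 at 30 sites, and 0.2 to 3.5 if only 10 contribute. A small-cluster correction or uneven site sizes would add to this. The ICC range and the 10-site case are assumptions.

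A separate limit should be kept in view. If online or referred respondents count towards the 100, people found through the campaign's own pages have already met the campaign. That would bias the awareness proportion, and no margin of error or design effect covers it.

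**What to change.** Keep the sample of 100 and make these changes:

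1. In Table 3, state the 95% level, label 10% as the best case for independent women, and give the range under an assumed ICC of 0.01 to 0.10: about 10 to 12 points at 20 sites, and up to about 13.5 if only 10 contribute. Say that these are normal-approximation figures and that the reported interval will be somewhat wider.
2. Reconcile the Recruitment and data-collection rows of Table 3 on who makes up the 100.
3. Record the recruiting site for each respondent.
4. Base the awareness estimate on women intercepted at sites. Calculate its interval with site as the cluster and a correction for the small number of clusters.
5. Report online and snowball respondents separately.

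The cost is some rewording, one extra survey field and a slightly less favourable stated precision. No additional participants are needed.

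### Engagement is compared across platforms on raw counts with no denominator, so a significant difference cannot be separated from a difference in audience or advertising exposure

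*Protocol article*

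**What the plan says.** All of the relevant text is in the protocol article.

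- **Definition of the outcome.** Under data collection and outcome measures, Table 3 (Outcome measures related to social media campaign) defines engagement as "Counts of retweets, likes, comments, link clicks, mentions, and direct messages received". Content sharing, which includes shares, is "Counts of testimonials, shares, reviews, guest posts, shared pictures at monthly intervals throughout the campaign".
- **The test.** The analyses row of Table 3 looks for "statistically significant differences in user engagement (e.g., number of likes, shares etc.) across different social media platforms". The methods it names are ANOVA and t-tests, with rank-based equivalents as the alternative. No rate, offset or covariate is named for this comparison.
- **Audience size.** "Counts of total followers, new followers" are recorded, overall and by month, but under audience characteristics and not as a denominator for engagement.
- **Denominators elsewhere.** Where the table intends a ratio it writes one out, as in "bounce rate (single-page sessions divided by the number of total sessions on the website".
- **Exposure.** The section Social media campaign describes "systematic advertising and promotion of iSISTAQUIT and video messages through various social media platforms", with Facebook, Instagram, LinkedIn and Twitter as examples. It does not say that audience, impressions or advertising volume will be equal across them. Impressions, reach and paid volume are not among the metrics listed in Table 3.

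**The concern.** The number of likes or shares that a platform collects depends on how many people saw the content and on how likely each viewer was to respond. The planned comparison is labelled a comparison of user engagement, but it is carried out on the product of the two. If one platform has more followers or more advertising, its counts will be higher even when viewers everywhere respond at the same rate. The non-parametric option deals with skewed counts, not with unequal exposure, because ranks shift with exposure just as means do.

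Evaluating the campaign is part of one of the three stated objectives, and Table 3 expects the metrics to show how effective it was with its audience. A significant result could be reported as better engagement on one platform when it shows only wider distribution there. The ordering could even be the reverse of the ordering of the rates.

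**Working it through.** **No stated figure to reproduce.** The article gives no sample size, power, significance level or audience size for this comparison. The check is therefore a reading of the definitions followed by an illustration.

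**Step 1: what the count measures.** For platform *j* in month *m*, expected count = *A_j* × *r_j*, where *A_j* is exposure and *r_j* is the engagement rate. If *r* is the same on all platforms, the ratio of expected counts for two platforms is *A_1*/*A_2*. Equal mean counts then require equal exposure, which the article does not state.

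**Step 2: inputs.**
- From the article: the campaign's research period runs from December 2021 to September 2022, which is 10 months; four platforms are named; metrics are summarised by month.
- Assumed: the month as unit of analysis; audiences as listed below; a true rate of 2% on every platform; two-sided 5% level.
- Assumed spread: count ~ Poisson(*A_j* × 0.02 × *G*), with *G* gamma distributed, mean 1 and coefficient of variation (CV) 0.3, 0.6 or 1.0.
- 2,000 simulated runs per setting.

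**Step 3: rejection on raw counts when all true rates are equal.** Each cell gives one-way ANOVA / Kruskal-Wallis.

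| Audiences | Mean monthly counts (*A* × 0.02) | CV 0.3 | CV 0.6 | CV 1.0 |
|---|---|---|---|---|
| 2000, 2000, 2000, 2000 | 40, 40, 40, 40 | 5.2% / 4.4% | 4.9% / 4.5% | 5.0% / 4.8% |
| 2400, 2000, 2000, 1600 | 48, 40, 40, 32 | 53.8% / 51.2% | 16.3% / 15.6% | 7.9% / 7.1% |
| 3000, 2000, 2000, 1000 | 60, 40, 40, 20 | 100% / 100% | 81.8% / 83.0% | 30.4% / 33.2% |
| 4000, 2000, 1000, 1000 | 80, 40, 20, 20 | 100% / 100% | 99.4% / 99.0% | 73.4% / 64.0% |
| 8000, 2000, 1000, 500 | 160, 40, 20, 10 | 100% / 100% | 100% / 100% | 98.0% / 97.8% |

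The first row confirms that both tests hold their level when exposure is equal. The other rows show that the rank test follows the ANOVA closely.

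**Step 4: the same data divided by audience size.** Over all settings, rejection is 3.6% to 5.4% for the ANOVA and 3.8% to 5.2% for Kruskal-Wallis.

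**Step 5: can the ordering reverse?** Platform 1 has an audience of 4,000 and a rate of 2%, so its mean count is 4,000 × 0.02 = 80. Platform 2 has an audience of 1,000 and a rate of 4%, so its mean count is 1,000 × 0.04 = 40. With 10 months and CV 0.6, the t-test on raw counts finds platform 1 significantly higher in 65% of runs, although its engagement rate is half that of platform 2.

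**The case against.** Several points on the other side deserve weight.

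- **Total engagement is a legitimate quantity.** The campaign aims at recognition, awareness and interest, and which platform produced most likes and shares is a fair descriptive question. This stands, and it is why raw counts should still be reported. It does not rescue a significance test presented as a comparison of engagement.
- **The wording leaves room.** Likes and shares are given as examples, and follower counts are collected. But the definitions in the same table are counts, and the article fixes both the outcome and the test. This is more than a detail left to a fuller plan.
- **Unequal exposure is not documented.** True: it is an assumption, though a plausible one. The point is that nothing makes exposure equal, not that the article shows it to be unequal.
- **The magnitude is not the protocol's own.** Also true. With mild imbalance and very variable counts the excess is small, about 8% against a nominal 5%.

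Three stronger readings are tempting, and the documents do not support them.

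- A reader might infer that the test measures audience size instead of engagement. A count contains both; the fault is that the two cannot be separated.
- A reader might infer that this test will steer campaign content. Table 3 ties content tailoring to the thematic analysis of text, not to this comparison.
- A reader might infer that the regression on the "relationship between the user characteristics (e.g., age, sex, region etc.) and social media metrics" has the same fault. Its outcome, unit and model are not given, some listed metrics (such as bounce rate) already carry denominators, and a regression could include exposure terms. The fault cannot be shown there.

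**Conclusion.** The point holds for the cross-platform comparison. As written, the plan tests raw counts across platforms whose exposure is not stated to be equal, so a significant result cannot be read as a difference in engagement. Choosing the non-parametric option leaves this unchanged.

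The size rests entirely on assumed audiences, rate and month-to-month spread. Within the unequal-audience settings examined, false rejection by the ANOVA runs from about 8% to 100%. The direction of the problem does not depend on those assumptions.

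It should be corrected, but it is of secondary weight. The comparison has no sample size or decision rule attached, and campaign success is judged on surveys and qualitative work as well as on metrics. The practitioner knowledge, attitudes and practices analysis is not affected.

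**What to change.** Compare engagement rates across platforms instead of counts.

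1. Divide counts by followers, which are already summarised by month, or by impressions or people reached where the commissioned metrics report can supply them.
2. Alternatively, fit a negative-binomial model to the counts with platform as a term and log exposure as offset. Flag paid and organic posts if that information is available.
3. Report raw counts descriptively as total engagement, and state that a difference in counts is not to be read as better engagement.

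The cost is one changed model and possibly one added field in the metrics report. Because the campaign has already launched, the media agency should be asked which exposure figures it can still provide. Followers are an imperfect denominator for paid content, which also reaches people who do not follow the account, so impressions or reach are preferable where they exist. If no usable exposure figure can be had, the platform comparison should be descriptive, without significance tests.
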